#### Subject-level analysis

Although the data for the primary outcome may not be normally distributed [16], the distribution of the mean would be normal according to the central limit theorem with a relatively large sample size. At the subject level, the outcome includes the percentage of children with no new caries developed over the study period as well as the mean number of new caries. Chi-square tests will be used to test the between-group differences in the proportion of subjects with new caries development and in the proportion of surfaces with new cavitations; *t* tests will be used to study the between-group differences in the mean number of new caries and in the increases in the numbers of nonvital teeth and of hypermobile teeth across the follow-up examinations. This research will also study if the treatment effects differ by patient characteristics (effect modification); the variables that may modify the treatment effects on the outcome variable include sex, baseline caries experience, treatment group assignment, oral hygiene habits, fluoride agent use, diet habits, snacking habits, dental visit behaviour, parental educational level, family income and family status (single- or both-parent households). As the outcome variable may not be normally distributed, Poisson or negative binomial regression will be considered to study the effect’s modification [21]. Aside from the primary outcome, *t* tests will also be performed to study the treatment’s effects on the number of arrested carious surfaces at the 30-month examination between the two groups.

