### Randomisation, treatment allocation and allocation concealment

The participating kindergarten children will first be categorised as either: 1) having an increased caries risk, which is defined as having caries experience (dmft >0); or 2) having a low caries risk with no caries experience (dmft = 0). The children will then be allocated by a stratified randomisation method at the subject level with two strata (increased and low caries risk) using a personal computer into the following two groups in blocks of eight children for fluoride treatment every 6 months: group SDF (38% SDF solution) and group NaF (5% NaF varnish). There will be no negative control group for ethical reasons. A statistician will keep the random number sequence, and opaque sealed envelopes will be used to conceal the allocation sequence until the interventions are assigned.

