### Sample size calculation

The mean number of cavitated teeth of a 3-year-old child was five in our previous study [16]. The mean number of new cavitated caries surfaces found in the 62 children in the SDF group was 0.47 (standard deviation (SD) 0.87), and the mean new cavitated caries surfaces in the 61 children in the NaF group was 0.70 (SD 0.84) at the 30-month review. This difference corresponded to a prevented fraction of 33% more in the SDF group when compared to the NaF group, which is considered clinically significant. With the statistical power set at 0.9 and type I error rate of 5% for a two-sided test, the required sample size would be 292 for each group. Considering a dropout rate of 20%, the total number of children to be recruited at baseline should be 365 in each group. Therefore, a total of 730 children need to be recruited at baseline examination for this trial.

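### Randomisation is stratified by baseline caries risk, but the named between-group tests ignore the stratum, which makes them somewhat conservative and gives up a little precision

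*Protocol article*

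**What the plan says.** The section on randomisation and allocation concealment has children "allocated by a stratified randomisation method at the subject level with two strata (increased and low caries risk"), in blocks of eight. The first stratum is described as "having an increased caries risk, which is defined as having caries experience (dmft >0"); the second is dmft = 0, called low risk. The protocol therefore treats the factor as prognostic.

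The Subject-level analysis section fixes the comparisons between arms. For means, *t* "tests will be used to study the between-group differences in the mean number of new caries". For children, "Chi-square tests will be used to test the between-group differences in the proportion of subjects with new caries development". No stratum term is attached to either. Baseline caries experience appears there only in the list of possible effect modifiers, and "Poisson or negative binomial regression will be considered to study the effect’s modification".

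The Discussion again treats dmft as an effect modifier and describes a regression to see whether risk factors relate to the outcome. The Surface-level analysis section allows for clustering of surfaces within a child but names no stratification factor. Nowhere is the treatment comparison itself adjusted for the stratum.

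**The concern.** Blocked randomisation within strata holds the arms close to balance on the stratum. Any outcome variation due to the stratum is then largely removed from the true sampling variation of the treatment difference. An unadjusted *t* or chi-square test does not know this: its standard error still contains the between-stratum variation. If dmft >0 predicts new caries, the reported interval is wider than it needs to be, the actual type I error falls below the nominal 5%, and some of the precision that stratification was meant to provide is not used.

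What is at stake is efficiency and correctly calibrated intervals. The estimate is not biased, and the error is on the cautious side.

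**Working it through.** **Inputs.** From the Sample size calculation section: means 0.47 (SD 0.87, 62 children) for SDF and 0.70 (SD 0.84, 61 children) for NaF; two-sided 5%; power 0.9; 292 per group; 20% dropout. From the Discussion: 22% ECC prevalence at age 3, used as a stand-in for the share of children with dmft >0. Not in the article and therefore assumed: R², the share of outcome variance that the stratum explains.

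**Step 1: the plan's own figure.** Difference 0.70 − 0.47 = 0.23. Pooled variance (0.87² + 0.84²)/2 = (0.7569 + 0.7056)/2 = 0.731, so SD = 0.855. The normal formula 2(1.960 + 1.282)² × 0.731/0.23² gives 291; the version based on the *t* distribution gives 292. Then 292/0.80 = 365 per group and 730 in total. The stated size reproduces, and it is the size for an unadjusted two-sample *t* test.

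**Step 2: effect of omitting the stratum.** With the arms balanced within strata, true SE = nominal SE × √(1 − R²). The nominal SE at 292 per group is 0.855 × √(2/292) = 0.0708, and 0.23/0.0708 = 3.25. Then:

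- true alpha = 2[1 − Φ(1.96/√(1 − R²))]
- unadjusted power = Φ((3.25 − 1.96)/√(1 − R²))
- adjusted power = Φ(3.25/√(1 − R²) − 1.96)
- adjusted n per group that matches the precision assumed in the plan = 292(1 − R²)

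| R² | SE too large by | True alpha | Power, unadjusted | Power, adjusted | Equivalent n per group |
|---|---|---|---|---|---|
| 0 | 0% | 5.0% | 90.1% | 90.1% | 292 |
| 0.02 | 1.0% | 4.8% | 90.4% | 90.7% | 287 |
| 0.05 | 2.6% | 4.4% | 90.7% | 91.5% | 278 |
| 0.10 | 5.4% | 3.9% | 91.3% | 92.9% | 263 |
| 0.20 | 11.8% | 2.8% | 92.5% | 95.3% | 234 |

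**Step 3: why the range stops at 0.20.** The average of the two means is 0.585. If counts within a stratum vary at least as much as a Poisson variable, the within-stratum variance is at least 0.585, so R² is at most (0.731 − 0.585)/0.731 = 0.20. With 22% of children at increased risk, a rate ratio of 2 between strata gives R² of about 0.05. A ratio of 3 gives stratum means 1.219 and 0.406 and R² = 0.22 × 0.78 × 0.813²/0.731 = 0.155. A ratio of 4 gives a between-stratum variance of 0.192, which would leave 0.731 − 0.192 = 0.539 within strata. That is below the mean of 0.585, so neither a Poisson nor a negative binomial model can produce it.

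**Step 4: simulation** (584 children, 22% at increased risk, blocks of eight, 3,000 runs per setting; unadjusted against stratum-adjusted):

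| Rate ratio | Type I, means | Power, means | Type I, proportions | Power, proportions |
|---|---|---|---|---|
| 1 | 5.8 v 5.8% | 91.2 v 91.3% | 5.2 v 5.2% | 78.6 v 78.6% |
| 2 | 4.5 v 5.0% | 90.4 v 91.2% | 4.6 v 5.0% | 76.6 v 78.4% |
| 3 | 3.6 v 5.5% | 86.6 v 89.6% | 4.3 v 5.4% | 73.5 v 76.2% |
| 4 (Poisson counts) | 2.2 v 5.1% | 91.4 v 95.3% | 2.9 v 4.7% | 75.4 v 80.2% |

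Simulation error is about 0.4 points on type I error and 0.5–0.8 points on power. The direction agrees with Step 2. The simulated outcome variance was not held at the pilot value. At ratio 3 the nominal SE was 0.0767 against the plan's 0.0708, which is why power there is below 90%. At ratio 4 the stratum explains 0.192/(0.585 + 0.192) = 25% of variance, beyond the range that the pilot figures allow.

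**The case against.** The strongest reply is that this is only an efficiency point. The unadjusted *t* test is simple, unbiased and the very test that the sample size was built on, and at the stated SD it keeps about 90% power or more. All of that stands.

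The gain may also sit at the low end. The sample size section says that children in the source study averaged five cavitated teeth, and the Background says that SDF in that study went only on decayed anterior teeth. Those children look like the increased-risk stratum, so their variance may hold little between-stratum variation. If the pilot mean and variance describe that stratum, and the low-risk rate is a half to a quarter of it with the same variance-to-mean ratio, R² is about 3–10%. This is also an assumption, but it is a reasonable one, and it falls inside the range used above.

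It can be said too that regressions containing both treatment and baseline caries are already planned. They are, but for effect modification and risk-factor association; they do not replace the named tests. An analysis plan could add the adjustment, but this article names the tests instead of leaving them open.

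A reader might infer more than the document supports:

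- **That false positives are inflated, the estimate is biased or the trial is too small.** The error runs the other way, and 292 per group reproduces.
- **That adjustment is worth a third more children.** This needs the rate ratio of 4, which the pilot variance cannot accommodate.
- **That Poisson regression is ruled out.** The SDF arm's variance-to-mean ratio is 0.7569/0.47 = 1.61, but the NaF arm's is 0.7056/0.70 = 1.01. The article leaves negative binomial open and offers either model only for effect modification.
- **That the *t* test misses the planned effect.** The calculation rests on the difference in means; the 33% prevented fraction is a restatement of it.
- **That an offset for surfaces at risk is required.** Randomisation balances their number in expectation, and the article also plans surface-level analyses.

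**Conclusion.** The point holds as a modest mismatch between design and analysis. The plan stratifies on a factor that it regards as prognostic and then names tests that ignore it. For R² of 0.02–0.20 the cost is a standard error about 1–12% too large, a true alpha of about 4.8–2.8%, and about 0–3 points of power for the mean comparison. In the simulations the loss for the child-level proportion was about 2–3 points at rate ratios of 2–3. If the stratum is not prognostic, nothing is lost.

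These figures assume a total SD of 0.855, 292 analysed children per group and balance within strata among those analysed. Dropout disturbs that balance somewhat, which would move the true alpha back towards 5%. The strength of prediction is an assumption throughout, because the article gives no rate ratio between strata. The direction does not depend on it.

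**What to change.** In the Subject-level analysis section, make the primary treatment comparison include the randomisation stratum:

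- **Mean number of new cavitated surfaces:** a linear model on arm and stratum with robust standard errors. This keeps the mean difference on which the sample size rests.
- **Proportion of children with new caries:** a Mantel-Haenszel test by stratum.
- **Unadjusted *t* and chi-square tests:** keep as supportive.
- **Optional:** if a prevented fraction is to be reported, a negative binomial model with robust standard errors and an offset for sound surfaces at baseline, labelled supportive because its summary measure is a rate ratio and not a mean difference.

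Specify this before the 18-month interim analysis, so that the choice to adjust cannot be influenced by results by arm.

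The cost is analysis wording only. The stratum is known at randomisation, no new data are needed and the sample size does not change.

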#### Surface-level analysis

To compare the differences in the time to develop cavitated carious lesions at the tooth surface level between the two treatment groups, a multilevel survival analysis will be adopted for the interval-censored data (because the time to develop the cavities cannot be observed exactly but falls within the interval between the two examinations). This analysis will account for the possible correlation (clustering) between the observations of multiple surfaces from the same child.

### Ethical consideration

Ethical approval has been sought from the Institutional Review Board of the University of Hong Kong/Hospital Authority Hong Kong West Cluster (HKU/HAHKW IRB) (UW18–619). Written consent will be obtained from the parents of each participating child. All of the participants will have the right to withdraw from the study at any time by informing the primary investigator. Withdrawal from the study will not influence the participants’ right to receive other services, such as oral health education. In general, the study will pose minimal risk to the participating children. Professional training will be provided to the field workers in order to minimise the risk. If one life-threatening case has been identified or more than 30% of the participants have severe systemic side effects, the trial will be stopped. All the personal information about potential and enrolled participants will be kept confidential in a personal computer. Only the investigators will have the right to access the dataset.

## Discussion

This is a phase II, single-centre, randomised, double-blind, active-controlled, parallel-group pragmatic trial that will assess the effectiveness of 38% SDF in preventing new carious lesions in primary anterior teeth. Because 5% NaF varnish is considered a standard of care for preventing ECC, we will use 5% NaF as a positive control group to assess whether 38% SDF is superior to this standard of care. There will be no negative control group in this study because every enrolled child should have the right to receive an effective preventative strategy. Since 38% SDF has a significantly higher fluoride concentration (44,800 ppm) than 5% NaF (22,600 ppm), our hypothesis is that 38% SDF will have a superior effect over 5% NaF in preventing ECC. If the results are as anticipated, this will help to change the standard of care. In addition, the results will be widely available and increase the adoption of SDF in other countries to reduce the global burden of ECC.

The latest survey found that ECC affected 55% of 5-year-old Hong Kong kindergarten children [3]. The ECC prevalence among 3-year-old kindergarten children was 22% [22]. A significant increase in ECC prevalence can be identified during the kindergarten life of Hong Kong children. Notably, 70% of the 5-year-old children suffering from ECC had their caries develop on their upper anterior teeth [3]. Therefore, we decided to provide a pragmatic intervention to prevent ECC progression by applying fluoride to children when they enter kindergarten (i.e. at 3 years old) and in the sites with high risk (i.e. upper anterior teeth).

This trial will be an outreach-based study. All of the clinical procedures will be performed in kindergartens. Therefore, the use of dental radiographs to detect dental caries is unavailable and unsafe under this setting. The examiner will use visual–tactile inspection without x-rays to assess the presence of carious lesions at baseline and the follow-up examinations, which other clinical caries studies have demonstrated to be practical and reliable [16, 20].

In this study, we assess the preventive treatment (38% SDF or 5% NaF) as the primary assessed independent variable regarding children’s ECC development. Apart from that, other clinical parameters, such as children’s caries experience (dmft index), will also be included as an effect modifier. Studies have reported that children’s oral health-related behaviours (toothbrushing frequency, use of fluoride products and bottle-feeding behaviours) and their socioeconomic status (family income and parental education level) are risk factors for the presence of ECC [3, 22]. Therefore, all of this information will be collected through a parental questionnaire survey, and those factors will be included in a regression analysis to see if they are related to the primary outcome (caries prevention effect).

We will use visual inspection to diagnose dental caries, rather than taking radiographs. Moreover, both SDF solution and NaF varnish have been approved as safe for clinical use, and the procedure of applying these treatments is noninvasive. Therefore, limited ethical concerns have been raised in this study, although the participants will be recruited at a young age. The participating children will enter primary school after this trial. They will receive dental care from the Department of Health through the School Dental Care Service.

## Trial status

This clinical trial was registered in ClinicalTrials.gov under the registration number NCT04075474 in September 2019. This protocol is version 2 developed on 14 January 2020. The recruitment for participation started on 18 September 2019. The anticipated date of recruitment completion is 31 January 2020.

## Data Availability

The data sets generated and/or analysed during the current study are available from the corresponding author on reasonable request. The results of each follow-up examination will be shared to each participant by a report to the parents. The interim and final results will be shared to other researchers by publications and presentations in international conferences.
